### Statistical Methods

#### Primary Outcomes

Procedural feasibility will be achieved if images of both the tumor and normal bladder are obtained in more than 60% of the patients. The feasibility based on OCT imaging will be assessed by determining the percentage of images suitable for diagnosis out of the total number of images obtained in all patients. A panel, consisting of 2 urologists and 1 PhD candidate, blinded to clinical information, will individually analyze the OCT images. They will determine if the OCT images are suitable for diagnosis. The OCT measurements will be scored as suitable if (1) tissue is observed on the OCT image, (2) the tissue is within the focus range of the OCT, and (3) no movement artifacts are observed in the image. In case of disagreement, an experienced research fellow will be added to the panel, and the scoring will be discussed within this panel. Consensus will be reached when 3 of the 4 panel members agree. The data will be described and presented as percentages with 95% CIs. No statistical tests will be performed.

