**Methods:**

This single-center feasibility study at Amsterdam University Medical Center includes patients undergoing TURBT for suspected bladder tumors. Eligible patients must be aged 18 years or older, have at least 1 cystoscopically accessible tumor, and must be physically fit for TURBT. Exclusion criteria include pregnancy, tumors larger than 2 cm, more than 5 tumors, isolated flat lesions, or tumors solely at the bladder neck. The primary end point assesses the procedural feasibility of OCT imaging, while the secondary end points evaluate tumor staging, grading, and correlation with histopathology. Up to 25 patients will be enrolled, with feasibility achieved if diagnostic images are obtained in more than 60% of the cases. OCT imaging is performed before and after tumor resection, with histopathological results used for comparison. Patients will be monitored for adverse events for 4 weeks after the procedure, after which study participation ends.

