### Study Outcomes

#### Primary End Point

The primary end point comprises two components:

Procedural feasibility of OCT imaging will be determined by the ability to generate images of the normal bladder wall and bladder tumors, as assessed by the operating urologist. Procedural feasibility will be achieved if diagnostic images of the tumor and normal bladder are obtained in more than 60% of the patients.Feasibility based on image use will be evaluated as the percentage of images suitable for diagnosis out of the total number of OCT images obtained. A percentage greater than 80% is regarded as feasible.

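### The patient-level primary criterion requires diagnostic images in the end point section but only images in the analysis section, and the suitability criteria are not tied to patient-level success.

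*Protocol article*

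**What the plan says.** The Primary End Point section states that "The primary end point comprises two components".

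- **Component 1, per patient.** The ability to generate images is judged "as assessed by the operating urologist". The success rule is "Procedural feasibility will be achieved if diagnostic images of the tumor and normal bladder are obtained in more than 60% of the patients".
- **Component 2, per image.** This is the share of all OCT images that are suitable for diagnosis. "A percentage greater than 80% is regarded as feasible".

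The Primary Outcomes paragraph of Statistical Methods restates component 1 as "Procedural feasibility will be achieved if images of both the tumor and normal bladder are obtained in more than 60% of the patients". For component 2 it says "A panel, consisting of 2 urologists and 1 PhD candidate, blinded to clinical information, will individually analyze the OCT images", and it gives three conditions for suitability: tissue is visible, the tissue is within focus range, and there is no movement artifact. Results are percentages with 95% CIs, without tests.

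The abstract's Methods paragraph gives one rule, "feasibility achieved if diagnostic images are obtained in more than 60% of the cases", and does not mention the 80% component. Sample Size and Enrollment stops inclusion at 15 patients with a feasible procedure, a term it does not define.

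**The concern.** Component 1 carries the same name and the same 60% threshold in both sections, but the event being counted differs. The analysis section is the outlier: the end point section, the abstract and the Conclusions all speak of diagnostic images. A patient with pictures of tumor and normal wall that nobody could read succeeds under the analysis wording and fails under the end point wording.

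Restoring the word is not enough, because *diagnostic* has no stated meaning where it decides patient-level success. The three suitability conditions belong to the panel and feed only the image percentage. Nothing stops a patient from counting toward the 60% when every one of that patient's images has failed panel review.

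The patient percentage is one of two results meant to support a larger trial, and the stopping count appears to rest on the same undefined success. Two analysts following different sections could report different values from the same data.

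**Working it through.** **1. The plan's own figure.** 0.60 × 25 = 15 reproduces the stopping count. (15/25 is exactly 60%, which is not more than 60%; with 25 patients the rule needs 16/25 = 64%. That is a separate matter, but 16 is the count used below.)

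**2. The wordings side by side.**

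| Place | What counts | Who judges | Criteria for diagnostic |
|---|---|---|---|
| Primary End Point, component 1 | diagnostic images of tumor and normal wall | operating urologist | none given |
| Statistical Methods, Primary Outcomes, component 1 | images of tumor and normal wall | not restated | not required |
| Abstract, Methods | diagnostic images | not stated | none given |
| Component 2, both sections | suitable images out of all images | blinded panel | three conditions |

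**3. Smallest share of suitable images that meets component 1.** Inputs: about 5 images per tumor and 3 of normal wall (OCT Measurements section) and 25 patients. Assumptions: one tumor per patient, and resection-bed images not counted. That gives 25 × 8 = 200 images.

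- Analysis wording: 0 of 200, provided images were obtained.
- Diagnostic wording, if one suitable image of each type is enough: 16 × 2 = 32 of 200, or 16%. The documents fix no number per patient; at least one of each is my assumption.
- Component 2: more than 0.80 × 200 = 160, so at least 161 of 200.

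**4. Illustration under the diagnostic wording.** Let s be the probability that an image is suitable. With independent images, the probability that a patient has at least one suitable image of each type is

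f(s) = [1 − (1 − s)^5] × [1 − (1 − s)^3].

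The probability of meeting component 1 is P(X ≥ 16) with X ~ Binomial(25, f).

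| s | f(s) | P(at least 16 of 25) |
|---|---|---|
| 0 | 0 | 0 |
| 0.2 | 0.672 × 0.488 = 0.328 | 0.0014 |
| 0.3 | 0.832 × 0.657 = 0.547 | 0.23 |
| 0.5 | 0.969 × 0.875 = 0.848 | 0.998 |

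f(s) reaches 0.60 at s ≈ 0.33. That is where the expected patient percentage equals the cutoff, not where passing becomes reliable.

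**5. Sensitivity to independence.** Focus and movement problems probably cluster within a patient. If all of a patient's images were suitable or none were, f(s) = s and the crossing moves to s = 0.60. In these two cases the patient criterion is met in expectation from s of 0.33 or 0.60, and the image criterion only above 0.80. Between those values the components give different answers.

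**The case against.** The strongest reply is that a reader might infer from all this that the trial as a whole could be declared feasible with few or no diagnostic images, and the documents do not support that. The inference needs the looser wording of the analysis section joined to the single rule of the abstract, yet the abstract itself says diagnostic. The end point section also makes panel-rated suitability above 80% part of the primary end point, and an omission from an abstract does not override that. Under the diagnostic wording, the illustration gives a pass probability of 0 at s = 0 and about 0.001 at s = 0.2. This reply stands.

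It is also fair to say that the two components answer different questions: whether images can be obtained during surgery, and what share of them is usable. Both are reported descriptively, and a split result is informative in a development-stage study. Requiring both for a single verdict, or replacing the operator's call altogether, would be a design preference. Nor do the documents call the operator unblinded; that follows from the operator performing the cystoscopy, and it is unavoidable for a judgment made during the procedure.

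None of this removes the conflict between the two definitions of component 1, or the missing link between the suitability criteria and patient-level success.

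**Conclusion.** The contradiction is in the text of a primary decision rule. It is not detail left to an analysis plan. As the analysis section is worded, component 1 can be met with no image suitable for diagnosis. As the end point section and abstract are worded, it cannot, provided the operator applies criteria like the panel's, which the article does not say.

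This conclusion rests on comparing the passages and needs no distributional assumption. The illustration adds only that, even with *diagnostic* restored, component 1 can be met while component 2 fails (for s from about 0.33 to 0.80 if images are independent, 0.60 to 0.80 if they cluster completely). The abstract's single rule therefore says less than a reader would take from it. Those ranges depend on one tumor per patient, 5 and 3 images, and at least one suitable image of each type.

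**What to change.** 1. In Statistical Methods, Primary Outcomes, restore *diagnostic* in the component 1 rule. Define it by the three existing conditions: at least one tumor image and at least one normal-wall image meet all three.
2. Report the patient-level percentage from the blinded panel's scores next to the operating urologist's call, each with a 95% CI.
3. Use the same definition for a feasible procedure in Sample Size and Enrollment, and say whose scoring counts toward the 15. If operator calls ran the count while panel scores defined success, inclusion could stop at 15 with fewer panel-confirmed successes.
4. In the abstract, name both components with their thresholds (more than 60% of patients, more than 80% of images) and report each separately. Meeting the 60% criterion alone should be described as procedural feasibility only.

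**Cost.** No new data are needed, because the panel is already due to score the images. The panel-based patient percentage may be lower than the operator's. The change is more than editorial: the article reports 16 participants enrolled and 13 procedures completed, and a clarified primary criterion may have to be notified as a substantial amendment. It should be fixed before panel results are known; if they are already known, the report should say so.

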#### Secondary Outcomes

The duration of OCT measurements (min) will be reported as medians with IQR. Tumor invasion based on OCT images will be determined by a panel of investigators. The panel will consist of 2 urologists, 1 PhD candidate, and 1 pathologist. The panel members will independently score the OCT images and classify them based on (1) whether there is a tumor present and (2) (if present) the tumor stage. In case of disagreement, an experienced research fellow will be added to the panel, and the scoring will be discussed within this panel. Consensus will be reached when 3 of the 5 members agree. The concluding tumor invasions will be descriptively compared to histopathological outcomes, with results presented as percentages with 95% CIs. Attenuation coefficients from OCT data will be analyzed and categorized into tumor grade categories, following the World Health Organization (WHO) 1973 and WHO 2016 grading systems. A descriptive comparison of OCT-based and histopathology-based tumor grades will also be displayed as percentages with 95% CIs. Associations between tumor stage and grade, as determined by OCT and histopathology, will be tested with chi-square or Fisher exact tests, as applicable. In addition, the panel will assess OCT images of the resection beds, reporting the percentage of evaluable images with 95% CIs. Finally, the urologist’s WLC-based estimates of tumor invasion and grade will be compared to OCT findings and histopathological results, and the association will be tested with chi-square or Fisher exact tests, as applicable.

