#### Secondary End Point

The secondary outcomes include (1) duration of the OCT measurements, (2) concordance between the OCT-based diagnosis of tumor invasion and histopathological diagnosis, (3) concordance between the OCT-based diagnosis of tumor grade and the histopathological diagnosis, (4) the ability of the OCT catheter to acquire evaluable images of the resection bed, and (5) concordance between intraoperative WLC assessments and OCT findings on tumor grade and invasion.

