### Conclusions

This trial aims to demonstrate the feasibility of using a newly designed MEMS-based OCT catheter and OCT system for the acquisition of diagnostic OCT images in human bladders. If the hypothesis is validated, it will lay the groundwork for a larger, multicenter trial to assess the diagnostic accuracy of OCT in staging and grading bladder cancer. The ultimate goal is to evaluate the potential role of this new OCT catheter and system as a real-time, noninvasive adjunct to standard cystoscopic assessment.

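### For tumor stage, OCT is a discussed panel consensus and WLC is one urologist's intraoperative estimate, so the OCT–WLC comparison mixes imaging method with number of readers

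*Protocol article*

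**What the plan says.** All references are to the protocol article.

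- **OCT stage** (Statistical Methods, Secondary Outcomes): "The panel will consist of 2 urologists, 1 PhD candidate, and 1 pathologist". Reading starts individually: "The panel members will independently score the OCT images and classify them", first for tumor presence and then for stage. After that, "In case of disagreement, an experienced research fellow will be added to the panel, and the scoring will be discussed within this panel", and "Consensus will be reached when 3 of the 5 members agree".
- **WLC stage** (Secondary End Point and Secondary Outcomes): the fifth secondary outcome is "concordance between intraoperative WLC assessments and OCT findings on tumor grade and invasion". The analysis text attributes the WLC estimate to the urologist and describes no panel, second reader or discussion for it.
- **Comparison** (Secondary Outcomes): the "WLC-based estimates of tumor invasion and grade will be compared to OCT findings and histopathological results", with chi-square or Fisher exact tests of association. OCT stage is also compared descriptively with histopathology.
- **OCT grade** (Secondary Outcomes) takes another route: "Attenuation coefficients from OCT data will be analyzed and categorized into tumor grade categories".
- **Longer-term role** (Conclusions): OCT as a "real-time, noninvasive adjunct to standard cystoscopic assessment".

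The limitations listed under Anticipated Findings do not mention the different number of readers behind the two stage calls.

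**The concern.** A majority of several readers can differ in accuracy from any one of them, whatever they are looking at. Here the OCT stage has been through four or five readers and a discussion, and the WLC stage has been through one. If OCT and WLC disagree on stage, or sit at different distances from histopathology, the plan cannot say how much comes from the imaging and how much from pooling readers.

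The comparison is a stated secondary objective, and both methods are set against the same histopathology, so readers of the report are likely to rank them. The sample size section says the findings will inform sample size calculations for later studies. A consensus figure carried forward as if it described one reader could mislead that planning.

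**Working it through.** **The plan's own figure.** The plan gives no reader accuracy, expected agreement, margin or power. The only design figure that can be derived is the enrollment stop: 0.60 × 25 = 15, which reproduces. The point does not depend on it.

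**Inputs.** From the plan: four initial readers, a fifth on disagreement, 3 of 5 decides, and one WLC reader. Assumed, because the plan gives no figures:

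- Stage is reduced to two categories.
- Every reader has the same accuracy p by either method, so OCT has no true advantage.
- p is 0.70 or 0.80.
- Discussion itself changes no votes.

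**Step 1: the consensus rule with independent errors.** The call is correct if all four are right, if three of four are right (the fifth cannot overturn them), or if two of four and the fifth are right:

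q = p⁴ + 4p³(1−p) + 6p²(1−p)²·p

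This equals the binomial probability of at least 3 of 5 correct.

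- p = 0.70: 0.2401 + 0.4116 + 0.1852 = 0.837, a gain of 13.7 points.
- p = 0.80: 0.4096 + 0.4096 + 0.1229 = 0.942, a gain of 14.2 points.

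**Step 2: shared errors.** Readers of the same image will tend to err together. Two models of that give:

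| Error model | q at p = 0.70 | Gain | q at p = 0.80 | Gain |
|---|---|---|---|---|
| Independent | 0.837 | 13.7 | 0.942 | 14.2 |
| Beta-binomial, correlation 0.2 | 0.765 | 6.5 | 0.872 | 7.2 |
| Beta-binomial, correlation 0.4 | 0.729 | 2.9 | 0.833 | 3.3 |
| Latent normal, correlation 0.5 | 0.744 | 4.4 | 0.854 | 5.4 |
| Latent normal, correlation 0.9 | 0.708 | 0.8 | 0.808 | 0.8 |

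The two correlation scales are not interchangeable, so rows should be compared only within a model.

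**Step 3: the planned outcome, OCT–WLC agreement.** If OCT and WLC errors are independent given the true stage, agreement is qp + (1−q)(1−p). With one OCT reader, q = p.

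- p = 0.70: single reader 0.49 + 0.09 = 0.58. Consensus with independent errors: 0.837 × 0.70 + 0.163 × 0.30 = 0.635, a shift of 5.5 points. At beta-binomial 0.4: 0.729 × 0.70 + 0.271 × 0.30 = 0.592, a shift of 1.2 points.
- p = 0.80: single reader 0.64 + 0.04 = 0.68. Independent errors: 0.942 × 0.80 + 0.058 × 0.20 = 0.765, a shift of 8.5 points. At beta-binomial 0.4: 0.833 × 0.80 + 0.167 × 0.20 = 0.700, a shift of 2.0 points.

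The shift is (2p − 1) times the accuracy gain, so it is smaller than the gain. At latent correlation 0.9 it is below 1 point (at p = 0.80, 0.6 × 0.8 = 0.5).

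**Step 4: direction.** At p = 0.40 with independent errors the rule gives q = 0.317, so pooling lowers OCT accuracy by about 8 points.

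**The case against.** A reader might infer that the plan builds in a spurious OCT advantage over WLC. The documents do not support that, for several reasons that stand.

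- **No superiority claim is planned.** The end point is concordance, tested as association. No difference in accuracy between OCT and WLC is to be tested. The accuracy gain matters only when the two comparisons with histopathology are read side by side.
- **Direction is open.** The accuracies are assumed. This catheter has not been studied in humans before, and structured training in reading its images is left to future studies, so accuracy below one half cannot be excluded. The panel mixes professions, and the WLC urologist sees the lesion live and in context, which may favour WLC.
- **The model is simpler than the call.** Stage is not dichotomised in the plan. With three or more categories, five readers can split 2-2-1 and reach no consensus.
- **Grade is not affected by panel pooling.** OCT grade comes from attenuation coefficients, not votes.
- **Precision is low.** With one tumor per patient (an assumption), a proportion of 0.70 has a 95% half-width of 1.96 × √(0.21/25) = 18 points with 25 patients and 23 points with 15. Both exceed the largest gain computed here.

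A reader might also infer that the study claims to test OCT as one urologist would use it live. It does not: the Conclusions give the adjunct role as an ultimate goal and leave diagnostic accuracy to a larger trial. That the panel reads stored images is itself inferred from the process described. Panel consensus is a legitimate way to explore what a new image can show.

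It can also be said that per-reader reporting is detail an article leaves to a fuller document. That does not dispose of the point, because the article itself fixes both sides of the stage comparison and fixes them unequally. Uncertain direction does not remove the confounding either.

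**Conclusion.** The point holds for tumor stage only. As written, the OCT–WLC stage comparison, and the placing of each beside histopathology, cannot separate imaging method from number of readers.

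The calculated ranges are illustrations resting on a dichotomised stage, equal readers with accuracy 0.70 to 0.80 by both methods, and no effect of discussion. The agreement range further assumes that OCT and WLC errors are independent given the true stage. They are not estimates of bias in this trial; the effect could be negligible or reversed.

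The matter concerns how one part of a secondary end point is interpreted. The primary end point is untouched. It is worth correcting because individual scores are already part of the planned process.

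**What to change.** For the stage part of the fifth secondary outcome, and wherever OCT and WLC stage are set side by side against histopathology:

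1. Report the independent pre-discussion stage score of each panel urologist, per reader and averaged, on the same numbered tumors that have a WLC estimate.
2. Show the panel consensus beside it, labelled as a consensus of four to five readers.
3. Leave grade as planned.
4. State that live WLC assessment versus reading of stored OCT images remains a difference between the methods, which this change does not remove.

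Fix the wording before OCT scores are compared with WLC or histopathology. It needs no new readers or reads, because members already score independently. The cost is a little more analysis and a single-reader OCT figure that may look less favourable than the consensus.

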#### OCT Measurements

During the standard TURBT procedure, the OCT measurements will be performed. After the inspection of the bladder and before the resection of the identified bladder tumors, the OCT catheter will be inserted through the working channel of the rigid resectoscope. The tumors will then be imaged with the OCT catheter tip at approximately 1 cm from the tumor. Approximately 5 measurements will be performed for each suspected lesion and tumor and 3 for a selected region of normal bladder wall. When the OCT measurements are finished, the OCT catheter is removed from the bladder, and the urologist will continue with the standard procedure. The resection of the tumors is performed according to standard care. However, the pathology specimens of each separate tumor will be collected and numbered according to the tumor numbers used during the OCT measurements and sent to the pathologist. After completion of the resection, the OCT catheter will be reinserted through the working channel of the rigid resectoscope, and approximately 3 OCT measurements will be performed on each resection bed. After these measurements, the OCT catheter will be removed from the bladder, and the urologist will continue with the standard procedure (Figure 1).

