### Sample Size and Enrollment

To date, no human study assessing the feasibility of this new MEMS-based OCT catheter for bladder cancer has been conducted. Therefore, a sample size calculation is not possible. The goal of this study is to test the technical and procedural feasibility of the device in a single-center, single-intervention, small prospective cohort study. In this IDEAL stage 2a study, up to 25 patients who undergo technically successful OCT measurements will be enrolled. Because the feasibility cutoff is set at 60%, inclusion will stop when a feasible procedure is performed in 15 patients. The findings of this study will inform sample size calculations for future investigations.

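### The OCT, cystoscopy and histopathology association tests assume independent units, but the plan names no unit and one patient can supply up to five matched tumors

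*Protocol article*

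**What the plan says.** Under Statistical Methods, Secondary Outcomes, the protocol article fixes the method for OCT against histopathology: "Associations between tumor stage and grade, as determined by OCT and histopathology, will be tested with chi-square or Fisher exact tests, as applicable". For the urologist's WLC estimates, these are "compared to OCT findings and histopathological results, and the association will be tested with chi-square or Fisher exact tests, as applicable". The section names no unit for either set of tests and does not mention several tumors or images from one patient.

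The design sections show what data arise:

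- **Tumors per patient.** The Eligibility Criteria require at least one suspected tumor and exclude patients with more than five, so a patient contributes one to five.
- **Matching.** Under OCT Measurements, "the pathology specimens of each separate tumor will be collected and numbered according to the tumor numbers used during the OCT measurements". OCT and pathology are therefore linked tumor by tumor.
- **Images per tumor.** "Approximately 5 measurements will be performed for each suspected lesion and tumor". Of the panel that judges invasion, Secondary Outcomes says: "The panel members will independently score the OCT images and classify them based on" tumor presence and stage.
- **Patients.** Under Sample Size and Enrollment, "up to 25 patients who undergo technically successful OCT measurements will be enrolled", and "inclusion will stop when a feasible procedure is performed in 15 patients".

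**The concern.** Pearson's chi-square test and Fisher's exact test count each entry in the table as a separate, independent piece of evidence. Tumors in one bladder may well share grade and stage. Their OCT readings share a session, a catheter and a tissue background. If both classifications cluster within patient, a few patients with several tumors can produce a table that looks associated even when OCT carries no information about the individual tumor.

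The Primary Outcomes section says that no tests are performed there, so these are the only hypothesis tests in the plan. The article presents the study as groundwork for a larger trial of diagnostic accuracy in staging and grading. A p-value that overstates the link between OCT and histopathology could colour how that trial is argued for.

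**Working it through.** The plan states no error rate, power or significance level for these tests, so there is no figure of its own to reproduce.

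**Inputs from the protocol article:** one to five tumors per patient, about five OCT measurements per tumor, 15 to 25 patients, chi-square or Fisher exact tests.

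**Assumed, because the document does not give them:** two-sided 5% level; ICC of each classification; distribution of tumors per patient; category prevalence; 2x2 tables.

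**Step 1, formula.** With tumors as the unit and no true association, the variance of the association statistic is inflated by

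DE = 1 + (m* - 1) x ICC_OCT x ICC_histology, where m* = E[m^2]/E[m] and m is the number of tumors per patient.

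The actual error rate is 2 x (1 - Phi(1.96/sqrt(DE))).

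- Mostly single tumors (60/20/10/5/5% with 1 to 5): E[m] = 1.75, E[m^2] = 4.35, m* = 2.49. At ICC 0.5 on both, DE = 1 + 1.49 x 0.25 = 1.37, giving 9.4%. At ICC 0.3 it is 6.6%; at 0.7, 13.6%.
- Counts uniform on 1 to 5: E[m] = 3, E[m^2] = 11, m* = 3.67. At ICC 0.5, DE = 1 + 2.67 x 0.25 = 1.67, giving 12.9%. At ICC 0.3 it is 7.8%; at 0.7, 19.7%.
- Only one classification clustered (ICC 0.7 and 0): DE = 1, giving 5.0%.

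The product of the two ICCs drives the result, so clustering is needed in both classifications.

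**Step 2, simulation of the planned choice of test.** The formula describes the chi-square test in large samples. At 15 to 25 patients Fisher's test will often apply, and it is conservative. The simulations took Fisher when any expected count was below 5 and chi-square otherwise, with OCT and histology generated independently of each other. With tumor counts of 1 to 5 in shares 40/25/15/10/10%, or 1 to 3 in shares 60/20/20%, the false-positive rates were:

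| Assumed ICC (both) | Assumed prevalence | False-positive rate |
|---|---|---|
| 0.3, or 0.5 with the rarer category | 50% or 20% at ICC 0.3; 20% at ICC 0.5 | about 2-7% |
| 0.5 | 50% | about 6-12% |
| 0.8 | 20% to 50% | about 5-19% |

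If patients with many tumors are more common, the rates rise. With counts uniform on 1 to 5 and prevalence 30% or 50%, they were 10.2-13.4% at ICC 0.5 and 16.5-20.3% at ICC 0.7.

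**Step 3, images as the unit.** All images of one tumor share one histology result, so ICC_histology = 1. Take one tumor with five images and an assumed OCT ICC of 0.2 to 0.5. Then DE = 1 + 4 x 0.2 = 1.8 to 1 + 4 x 0.5 = 3.0, and the formula gives about 14% to 26%.

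**Step 4, one tumor per patient.** Under the same null, Fisher's test rejected in 1.4-4.3% of simulated trials and chi-square in 4.0-5.7%. The inflation disappears.

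**The case against.** A reader might infer that the protocol knowingly treats tumors as independent and that its false-positive rate is therefore about twice the nominal 5%. The document supports neither part.

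- **The unit is inferred.** The specimen-numbering rule fixes how OCT and pathology are matched, not how the tables are filled. With one result per patient the problem would vanish. A condensed article may also leave the unit to a fuller document.
- **The doubling is one scenario.** It needs an ICC near 0.5 in both classifications, a fair share of patients with several tumors, and roughly balanced categories. At ICC 0.5 with counts of 1 to 5 in shares 40/25/15/10/10%, moving prevalence from 50% to 20% lowers the rate from 9.8-10.8% to 4.7-6.1%.
- **Little depends on it.** This is a feasibility study with no sample size calculation. The secondary end points are concordances reported as percentages with 95% CIs, and no success criterion uses these p-values.

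All three limit the size and weight of the point, but they do not remove it. The tests are a stated choice, not a detail left open. The readings that the text supports, tumor or image, both produce dependent units. One result per patient is nowhere stated and would set aside the tumor-by-tumor matching that the procedure builds in.

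**Conclusion.** The point holds as a mismatch between named tests and design: independence-based tests are prescribed, the unit is not stated, and the data are tumors (and images) nested in patients. The error is in the direction of p-values that are too small if tumors are the unit and both classifications cluster within patient. Its size is unknown from the document. Under the assumptions above it runs from no inflation, or even a conservative test, to roughly four times nominal, and could be larger with images as the unit. It stays near 5% or below if clustering is weak, is present in only one classification, or the categories are unbalanced at moderate ICC. The figures rest on 2x2 tables; stage and grade may have more categories. Because the tests are secondary and exploratory, severity is minor.

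**What to change.** In Secondary Outcomes, state that the tumor is the unit of description, with one OCT classification per tumor rather than per image, and that the patient is the independent unit. Then replace the plain tests with one of these, for both the histopathology and the WLC comparisons:

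- a permutation test that reassigns whole patients, keeping each patient's tumors together. Because tumor counts differ, the rule for exchanging patients needs to be prespecified;
- a cluster-adjusted score test that sums each patient's contribution and uses the between-patient variance. It held 2.8-4.8% in the settings with 50% prevalence, but becomes very conservative with few patients and rare categories (down to 0.2-1%);
- a Fisher exact test on one prespecified index tumor per patient, either as the main test or as a sensitivity analysis.

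This changes analysis wording only and needs no new data or readers. The price is somewhat larger p-values and, for the index-tumor analysis, fewer tumors used.
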